## Abstract

**Objectives:**

To assess the efficacy of ivermectin in addition to standard treatment compared to standard treatment alone in reducing hospitalizations in the COVID-19 patient population.

**Trial design:**

IVERCOR-COVID19 will be a single-center, prospective, randomized, double-blind, parallel group (1:1 ratio), placebo-controlled study.

**Participants:**

Patients who meet the following criteria will be invited to participate:

Inclusion criteria: (1) Over 18 years of age who reside in the province of Corrientes at the time of diagnosis. (2) Confirmed diagnosis of COVID-19 by polymerase chain reaction (PCR) test for detection of SARS-CoV2 in the last 48 h. (3) In the case of women of childbearing age, they must be using a contraceptive method of proven efficacy and safety (barrier, hormonal, or permanent contraceptives) for at least 3 months prior to inclusion in the present study and for the entire period of time for the duration of the study and until at least 30 days after the end of this study. A woman will be considered to have no reproductive capacity if she is postmenopausal (at least 2 years without her menstrual cycles) or if she has undergone surgical sterilization (at least 1 month before the time of inviting her to participate in this study). (4) Weight at the time of inclusion greater than 48 kg. (5) That they sign the informed consent for participation in the study.

Exclusion criteria: (1) pregnant or breastfeeding women; (2) known allergy to ivermectin or some of the components of ivermectin tablets or placebo; (3) current use of home oxygen; (4) require hospitalization due to COVID-19 at the time of diagnosis or history of hospitalization for COVID-19; (5) presence of mal-absorptive syndrome; (6) presence of any other concomitant acute infectious disease; (7) known history of severe liver disease, for example liver cirrhosis; (8) need or use of antiviral drugs at the time of admission for another viral pathology other than COVID-19; (9) need or use of hydroxychloroquine or chloroquine; (10) use of ivermectin up to 7 days prior to randomization; (11) patients on dialysis or who have required it in the last 2 months or who plan to do it in the next 2 months; and (12) current participation or in the last 30 days in a research study that has included the administration of a drug (Table 1).

**Table 1 Tab1:** Ivermectin/placebo dose according to patient weight

Patient weight	Ivermectin/placebo dose	Total dose (mg)
Equal to or greater than 48 kg and less than 80 kg	2 tablets of 6 mg each at the time of inclusion and 2 tablets 24 h after the first intake	24
Equal or greater than 80 kg and less than 110 kg	3 tablets of 6 mg each at the time of inclusion and 3 tablets 24 h after the first intake	36
Equal or greater than 110 kg	4 tablets of 6 mg each at the time of inclusion and 4 tablets 24 h after the first intake	48

The study will be carried out by the Ministry of Public Health of the Province of Corrientes (Argentina) in coordination with the Institute of Cardiology of Corrientes in the Province of Corrientes, Argentina.

**Intervention and comparator:**

Intervention group: patients who are randomized to ivermectin will receive the dose according to their weight (patients up to 80 kg will receive 2 tablets of 6 mg ivermectin; patients with more than 80 kg and up to 110 kg will receive 3 tablets of 6 mg of ivermectin; patients weighing more than 110 kg will receive 4 tablets of 6 mg ivermectin) the day they enter the study and the same dose 24 h after the first dose.

Control group: patients who are randomized to placebo will receive the dose according to their weight (patients up to 80 kg will receive 2 tablets of 6 mg placebo; patients with more than 80 kg and up to 110 kg will receive 3 tablets of 6 mg of placebo; patients weighing more than 110 kg will receive 4 tablets of 6 mg placebo) on the day they enter the study and the same dose 24 h after the first dose (Table 2).

**Table 2 Tab2:** Inclusion and exclusion criteria

Inclusion criteria	Exclusion criteria
1. Over 18 years of age who reside in the province of Corrientes at the time of diagnosis	1. Pregnant or breastfeeding women
2.Confirmed diagnosis of COVID-19 by polymerase chain reaction test for detection of SARS-CoV2 in the last 48 h	2. Known allergy to ivermectin or some of the components of ivermectin tablets or placebo
3. In case of being women of childbearing age, they must be using a contraceptive method of proven efficacy and safety (barrier, hormonal, or permanent contraceptives) for at least 3 months prior to inclusion in the present study, during the entire period of time for the duration of the study, and until at least 30 days after the end of this study. A woman will be considered to have no reproductive capacity if she is postmenopausal (at least 2 years without her menstrual cycles) or if she has undergone surgical sterilization (at least 1 month before the time of inviting her to participate in this study)	3. Current use of home oxygen
4. Weight at the time of inclusion equal to or greater than 48 kg	4. That require hospitalization due to COVID-19 at the time of diagnosis or history of hospitalization for COVID-19
5. That they sign the informed consent for participation in the study	5. Presence of mal-absorptive syndrome
	6. Presence of any other concomitant acute infectious disease
	7. Known history of severe liver disease, for example liver cirrhosis
	8. Need or use of antiviral drugs at the time of admission for another viral pathology other than COVID-19
	9. Need or use of hydroxychloroquine or chloroquine
	10. Use of ivermectin up to 7 days prior to randomization
	11. Patients on dialysis or who have required it in the last 2 months or who plan to do it in the next 2 months
	12. Current participation or in the last 30 days in a research study that has included the administration of a drug

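### The dosing text and Table 1 give different tablet counts at exactly 80 kg and 110 kg, and the two versions of the weight criterion disagree at exactly 48 kg

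*Protocol article*

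**What the plan says.** The article states the weight-based dosing rule in two places.

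- **Table 1 (under Participants)** includes the lower limit of each band. The bands are "Equal to or greater than 48 kg and less than 80 kg" (2 tablets per intake, 24 mg in total), "Equal or greater than 80 kg and less than 110 kg" (3 tablets, 36 mg) and "Equal or greater than 110 kg" (4 tablets, 48 mg).
- **The text under Intervention and comparator** includes the upper limit of each band. Its lowest band is worded "patients up to 80 kg will receive 2 tablets of 6 mg ivermectin". The middle band, which leaves out its lower limit, is given as "patients with more than 80 kg and up to 110 kg will receive 3 tablets of 6 mg of ivermectin". The top band then starts only above its cut-off: "patients weighing more than 110 kg will receive 4 tablets of 6 mg ivermectin". The control-group paragraph repeats the same limits for placebo.

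It also states the weight criterion for entry twice. Inclusion criterion 4 in the Participants text reads "Weight at the time of inclusion greater than 48 kg". Criterion 4 in Table 2 reads "Weight at the time of inclusion equal to or greater than 48 kg".

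Each dose is taken twice, on the day of entry and 24 hours later. Table 3 schedules an adherence check at visits 1 and 2. Under Full protocol, the article describes itself as a summary and refers to an additional file that is not shown.

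**The concern.** A weight-banded dose should give one tablet count for every eligible weight. Here the two statements place the equality sign on opposite sides of each cut-off, so they differ at exactly 80 kg and exactly 110 kg. The text uses its version for all three bands and in both arms, so it reads as a second complete rule and not as a single slip. The entry criterion has the same kind of conflict at 48 kg.

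These are round values that occur in practice if weight is recorded in whole kilograms. For a patient on a boundary, whoever follows one statement breaches the other. Three things then have two answers in the article: the dose to dispense, the tablet count against which adherence is judged, and whether a 48 kg patient is a valid participant or an eligibility deviation.

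**Working it through.** **1. Reproduce the totals in Table 1.** Inputs from Table 1 are the tablets per intake (2, 3, 4), 6 mg per tablet and two intakes.

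Total dose = tablets × 6 mg × 2:
- 2 × 6 × 2 = 24 mg
- 3 × 6 × 2 = 36 mg
- 4 × 6 × 2 = 48 mg

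All three stated totals reproduce, so the fault lies in the cut-offs and not in the dose arithmetic.

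**2. Apply both rules at and around each cut-off.**

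| Weight (kg) | Table 1 total | Text total | Eligible, Participants text | Eligible, Table 2 |
|---|---|---|---|---|
| 47.9 | none | 24 mg | no | no |
| **48** | 24 mg | 24 mg | **no** | **yes** |
| 48.1 | 24 mg | 24 mg | yes | yes |
| 79.9 | 24 mg | 24 mg | yes | yes |
| **80** | **36 mg** | **24 mg** | yes | yes |
| 80.1 | 36 mg | 36 mg | yes | yes |
| 109.9 | 36 mg | 36 mg | yes | yes |
| **110** | **48 mg** | **36 mg** | yes | yes |
| 110.1 | 48 mg | 48 mg | yes | yes |

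The row at 47.9 kg is no conflict, because both versions of the criterion exclude that patient. The disagreements are confined to 48, 80 and 110 kg.

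**3. Size of the dose difference.** It is one 6 mg tablet per intake, or 12 mg in total, at both cut-offs. Relative to the lower figure, this is 36/24 = 1.50 (50% more) at 80 kg and 48/36 = 1.33 (33% more) at 110 kg.

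**4. How many patients could be affected.** The documents give neither the weight distribution nor the recording precision, so these inputs are assumptions: normal weights, mean 75 to 85 kg, SD 15 to 18 kg. The planned total of 500 is from the article.

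Share at a recorded weight w = Φ((w + h − mean)/SD) − Φ((w − h − mean)/SD), where h is half the recording unit.

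Recorded to 1 kg (h = 0.5):
- Lowest in the range (mean 75, SD 18): at 80 kg, Φ(0.306) − Φ(0.250) = 0.6200 − 0.5987 = 2.13%; at 110 kg, Φ(1.972) − Φ(1.917) = 0.9757 − 0.9724 = 0.33%. The sum is 2.47%, and 500 × 0.0247 = 12.3 patients.
- Highest in the range (mean 85, SD 15): at 80 kg, Φ(−0.300) − Φ(−0.367) = 0.3821 − 0.3569 = 2.52%; at 110 kg, Φ(1.700) − Φ(1.633) = 0.9554 − 0.9488 = 0.66%. The sum is 3.18%, and 500 × 0.0318 = 15.9 patients.

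Recorded to 0.1 kg (h = 0.05), the shares fall tenfold, to 0.247% and 0.318%, or 1.2 to 1.6 patients of 500.

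With 1:1 allocation, about half of the 12 to 16 (6 to 8) would be on ivermectin. On the same assumptions, the share at exactly 48 kg is 0.1% to 0.7% when weight is recorded to 1 kg. A preference for round numbers when weights are recorded would raise the counts at 80 and 110 kg.

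**The case against.** The strongest reply is that this is a wording slip at three points on a continuous scale. The two rules agree at every other eligible weight checked. The limits are the same for ivermectin and placebo, so the ambiguity does not differ by arm, does not reveal allocation, and leaves randomization, the primary outcome and the sample size untouched. This stands, and it is why the point is not graded as critical.

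A reader might go further than the documents allow in three ways.

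- **That dose, adherence and deviation status could not be determined in the trial.** The article is a summary, and the full protocol may hold a single rule. What can be said is that this article gives two.
- **That patient safety is compromised.** Each competing dose is one that both versions give to patients just above or just below the cut-off, and the article states no safety threshold that either reading would cross.
- **That a fixed, sizeable number of patients is affected.** The count depends on an undocumented recording precision and drops to 1 or 2 if weight is taken to 0.1 kg.

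It can also be said that the 48 kg conflict is the weakest of the three, since both tables include that weight and only the sentence under Participants excludes it. That is fair, but agreement between two tables does not show which version governs entry.

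The reply does not remove the contradiction. All the statements are current text in version 1.0, none is an extraction fault, and nothing in the article says which takes precedence. This is also not detail left to the full protocol: the article states both rules itself.

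**Conclusion.** The concern holds as an internal inconsistency of moderate severity. At exactly 80 kg and 110 kg, the text and Table 1 differ by one tablet per intake (24 against 36 mg, and 36 against 48 mg in total). At exactly 48 kg, eligibility has two answers. These facts rest on the wording alone and need no assumption.

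The reach is small and uncertain. Under the assumed weight distribution, 2.5% to 3.2% of patients (about 12 to 16 of 500) fall on 80 or 110 kg if weight is recorded to 1 kg, and about 1 to 2 of 500 if it is recorded to 0.1 kg. Bias between arms, loss of blinding and an effect on the sample size do not follow from it. What remains is that boundary patients have no single dose, adherence reference or eligibility status in this article.

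**What to change.** Reconcile the following, after checking each against the full protocol:

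1. The weight limits in the Intervention and comparator text, for both the ivermectin and the placebo paragraph, with those in Table 1, so that each weight maps to one tablet count wherever it is stated.
2. Inclusion criterion 4 in the Participants text with criterion 4 in Table 2 and the lowest band of Table 1, so that 48 kg has one eligibility status.

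The clinical team must decide which version stands; the documents do not show which was intended, and none is proposed here. Adherence and eligibility deviations should then be classified against the reconciled version.

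The cost is one clarifying amendment and a note to the staff who screen and dispense. No change to the sample size or the design is needed.

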**Main outcomes:**

Primary outcome will be the percentage of hospitalizations in patients with COVID-19 in the intervention and control groups.

Secondary outcomes: time to hospitalization in each of the arms of the study: number of days elapsed from the inclusion in the study until the hospitalization of the patient; percentage of use of invasive mechanical ventilation in each of the study arms: every patient who is connected to invasive mechanical ventilation after signing the informed consent and before the final study visit; time to invasive mechanical ventilation in each of the arms of the study: number of days elapsed from inclusion in the study to connection to invasive mechanical ventilation of the patient; percentage of patients requiring dialysis in each of the study arms: all patients who require renal replacement therapy of any kind, temporary or permanent, and which begins after signing the informed consent and before the final visit; mortality from all causes in each of the two trial groups: death of the patient, from any cause. Negative PCR swab at 3 ± 1 and 12 ± 2 days after entering the study.

Ivermectin safety: it will be analyzed according to the incidence of adverse events that patients present in the intervention and control groups.

The end of study (EOS) is recorded as the day the patient is discharged or death. Discharge will be granted according to the current recommendations of the Ministry of Public Health of the Province of Corrientes. A follow-up visit (EOF) will be made by phone 30 days after the EOS when vital status will be verified.

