**Numbers to be randomized (sample size):**

We will include a total of 500 patients (250 patients in each group).

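### The primary outcome counts hospitalization only, so a patient who dies without admission is counted the same as one who recovers at home

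*Protocol article*

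**What the plan says.** All of this is in the Protocol article.

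- **Objective** (Objectives): efficacy of ivermectin plus standard treatment "compared to standard treatment alone in reducing hospitalizations in the COVID-19 patient population". Death is not named.
- **Primary outcome** (Main outcomes): "Primary outcome will be the percentage of hospitalizations in patients with COVID-19 in the intervention and control groups".
- **Death** (Main outcomes, secondary outcomes): "mortality from all causes in each of the two trial groups: death of the patient, from any cause".
- **End of observation** (Main outcomes): "The end of study (EOS) is recorded as the day the patient is discharged or death".
- **Later contact** (Main outcomes): "A follow-up visit (EOF) will be made by phone 30 days after the EOS when vital status will be verified".
- **Setting at entry** (Participants, exclusion criterion 4): patients are excluded if they "require hospitalization due to COVID-19 at the time of diagnosis or history of hospitalization for COVID-19".
- **Size** (Numbers to be randomized): 500 patients, 250 per arm.

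Nothing in the article makes the primary outcome a composite with death, and nothing says that a death without admission counts as a primary event.

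**The concern.** Hospitalization is used here as the marker that an outpatient's disease has become worse. Death without admission is a worse outcome than hospitalization, and it also makes hospitalization impossible. Under the stated definition it falls on the favourable side of the primary comparison. If one arm has more such deaths than the other, that arm's hospitalization percentage looks better than its patients' course justifies. The primary estimate would then mix the effect on admissions with the effect of deaths that prevented admission.

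**Working it through.** **Inputs.** The documents give 250 patients per arm. They give no hospitalization rate, alpha or power in this article, and no expected number of deaths before admission. The rates below (about 5% to 20% in control), the two-sided 5% level and the 80% power are therefore assumptions, used for scale only. The stated sample size cannot be reproduced from the article and is not in dispute.

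**Step 1: how one death is counted.** Let H be the patients hospitalized and D the patients who die without admission, per arm.

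- Stated primary outcome: H / 250.
- Hospitalization or death without admission: (H + D) / 250.

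A death without admission adds 0 to the numerator and 1 to the denominator of the stated outcome, the same as a recovery at home. Each one opens a gap of 1/250 = 0.4 percentage points between the two definitions; three would make 3/250 = 1.2 points.

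**Step 2: effect on the comparison.** Subtracting the arms, the difference in percentages under the two definitions differs by (D_ivermectin − D_control) / 250. If the two numbers are equal, the difference is unchanged. An imbalance of one death moves it by 0.4 points.

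**Step 3: scale against a detectable effect.** The ivermectin percentage needed for 80% power with 250 per arm, two-sided 5%:

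| Assumed control | Detectable ivermectin | Difference | 0.4 points as share |
|---|---|---|---|
| 5% | 0.8% | 4.2 points | 9.5% |
| 10% | 3.7% | 6.3 points | 6.3% |
| 15% | 7.15% | 7.85 points | 5.1% |
| 20% | 11.0% | 9.0 points | 4.4% |

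A one-death imbalance is thus about 4% to 10% of the difference that the trial could detect.

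**Step 4: effect on the test, at the boundary.** Pooled two-sided z test: z = (difference in proportions) / √(2p(1−p)/250), where p is the pooled proportion. For each control count, the ivermectin count is the largest that is still significant.

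| Hospitalized, control vs ivermectin | p | One ivermectin death counted | One death counted in each arm |
|---|---|---|---|
| 13 vs 4 | 0.026 | 13 vs 5, p = 0.055 | 14 vs 5, p = 0.035 |
| 25 vs 13 | 0.043 | 25 vs 14, p = 0.067 | 26 vs 14, p = 0.048 |
| 38 vs 23 | 0.040 | 38 vs 24, p = 0.058 | 39 vs 24, p = 0.043 |
| 50 vs 33 | 0.041 | 50 vs 34, p = 0.056 | 51 vs 34, p = 0.043 |

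These rows were chosen at the edge of significance, so the third column shows only that one uncounted event can matter there; it is not a forecast. The last column confirms Step 2: equal deaths leave the difference as it was. The p-value rises a little because the pooled variance rises, and a ratio measure would move slightly towards 1 (13/25 = 0.52 becomes 14/26 = 0.54).

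**The case against.** The endpoint matches the stated objective, which is to reduce hospitalizations, so the document does not contradict itself. Deaths are also not hidden: all-cause mortality is reported, death is recorded as end of study, and vital status is checked by phone 30 days later. The article is a summary, and the full protocol may say how deaths before admission are handled.

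Part of this stands. A mortality imbalance would be visible next to the primary result. But separate reporting leaves the primary estimate as it is. A rule in the full protocol that counted these deaths would depart from the endpoint that the article states outright; if one exists, the sponsor need only point to it.

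A reader might infer more than the documents support:

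- **That the plan declares such a death a treatment success.** The article has no such term. The patient is simply not hospitalized.
- **That later care-seeking in one arm would bias the result.** The trial is randomized and placebo-controlled, and participants, investigators, care providers and outcome assessors are blinded. Care-seeking driven by allocation is unlikely. What remains is chance or a drug effect on death before admission, and the documents give no evidence of the latter.
- **That one to three such deaths in an arm, set against an assumed 25 hospitalizations (4% to 12%), measure the bias.** Neither figure comes from the documents, and bias in the difference depends on the imbalance between arms, which may be zero.

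**Conclusion.** The point holds as a weakness in how the primary outcome is fixed: a death without admission is counted like a recovery at home. This follows from the stated definition and needs no assumption about rates. Its effect on the result is uncertain and probably small: 0.4 percentage points per death in an arm, and a shift in the difference between arms only where the numbers of such deaths are unequal. Under assumed control rates of 5% to 20%, an imbalance of one is about 4% to 10% of the difference detectable with 80% power, so it could decide a borderline result but not a clear one. The documents do not support the stronger conclusion that the primary result will be biased, or that it will favour ivermectin.

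**What to change.** Define the primary outcome as hospitalization or death from any cause without prior admission, over the existing follow-up to end of study. Report hospitalization alone and death as components. If the registered primary outcome must stay, prespecify this composite as the key sensitivity analysis before unblinding.

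Cost: an amendment and a registry update (the amendment and a statement of the sensitivity analysis if the primary stays), and a few deaths unrelated to COVID-19 among the events. Over the window to end of study, death is already recorded.

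A reader might think that the window could be extended, for example to day 30, with no new data. The article does not support that. It describes the end-of-follow-up call as a check of vital status. Table 3 marks an endpoint evaluation at that call without saying what it covers, and the last visit with a fixed day is at 12 ± 2 days. Before any extension, confirm that admissions after end of study are ascertained at the call.

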**Randomization:**

Randomization will be done through a web system with randomly permuted blocks. Randomization will be carried out by one of the investigators who will not participate in the inclusion of patients or in the delivery of medication (Table 3).

**Table 3 Tab3:** *EOS* end of study, *EOF* end of follow-up

Visit	Basal and randomization, day 0	Day 3 ± 1	Day 12 ± 2		
	V#1	V#2	V#3	EOS	EOF
Informed consent	X	–	–	–	–
Inclusion/exclusion criteria	X	–	–	–	–
Demographic data and medical history	X	–	–	–	–
Concomitant medication	X	–	–	–	–
Vital signs*	X	X	–	–	–
Anthropometric data^^^	X	–	–	–	–
Basal laboratory	X	–	–	–	–
PCR swab	–	X	X	–	–
Assessment of adverse events	–	X	X	X	–
Final objective evaluation	–	X	X	X	X
Randomization	X	–	–	–	–
Adherence to treatment	X	X	–	–	–

*Includes heart rate, temperature, and oxygen saturation by a digital saturometer

^Includes weight and height

